#### ***Questionnaire for injured runners***

When an RRI is registered in the web-based training log, a questionnaire will be automatically sent to the participant after two weeks. This questionnaire is used to specify medical/paramedical treatment, the order of treatments, type and frequency of the treatment, medical aids, and absence from work, school or training due to the RRI. Injured runners are asked to specify the injury location, if the injury is new or recurrent, what structure is injured (e.g. muscle, tendon, bone or ligament), and the injury mechanism (e.g. strain, sprain, rupture, dislocation, contusion, inflammation or overuse). When the runner is seen by a professional, a diagnosis will be asked. Until recovery from the RRI, every four weeks a follow-up questionnaire on medical/paramedical consumption and absence from work, school or training is sent to the injured runner.

To validate the RRI registration method that is used in this study, approximately 10% of the subjects who sustain an RRI will be contacted by a sports physician. The sports physician will perform a standard physical examination and will then complete the abovementioned RRI questionnaire regarding location, structure, and mechanism of the injury.

#### ***RRI cost analysis***

From the data derived from the RRI questionnaire and subsequent follow-up questionnaires, direct and indirect costs will be calculated. Costs will also be calculated from a societal perspective. Direct healthcare costs will include costs resulting from medical/paramedical treatment and/or medical aids. Indirect costs will include costs resulting from absence from paid work or unpaid work, as well as leisure time lost. Dutch guideline prices will be used to value resource use [33]. Direct costs of hospital treatment will be estimated on the basis of standard prices from the Health Care Insurance Board [34]. The costs of medication and medical aids are estimated on the basis of prices recommended by the Royal Dutch Society of Pharmacy [35] and the Health Care Insurance Board [34,36]. Costs of loss of productivity due to absenteeism from paid or unpaid work will also be included. Costs of absenteeism from paid work are estimated using the friction cost approach with a friction period of four months and based on the mean age- and sex-specific income of the Dutch population. [33]. Costs of productivity loss attributable to unpaid work, such as study and household work, will be estimated at a shadow price of EUR 8.78/hour. All prices are standardized to the year 2012 and will be adjusted for inflation [36]. Total costs will be estimated for each injured athlete by multiplying resource data by cost prices. Total, direct and indirect costs will be calculated by adding costs per category of utilization of healthcare resources.

### Statistical analyses

Incidence of RRIs will be calculated for all participants and for male and female participants separately as the number of new injuries reported per 1000 hours of running exposure. Exposure time (in hours of running exposure) will be calculated from the time the participant started the running program until an RRI is reported (injured runners) or until the end of the program (non-injured runners).

Descriptive data will be presented as means (± s.d.) and frequency distributions.

For identification of risk factors for RRIs only data from the baseline questionnaire and the running log will be used. Data of the follow-up questionnaires will not be used for this purpose, because these data do not contribute to a pre-running risk-profile. It is possible for a single subject to sustain multiple RRIs during the study period. In this case only the occurrence of the first RRI will be used for analysis. Potential risk factors for RRI will be entered into a multivariate Cox regression prediction model. Hazard ratios and the corresponding 95% confidence intervals will be calculated for the factors associated with RRI.

Data of the baseline and follow-up questionnaires will be compared with a repeated-measures ANOVA to examine the health effects of participating in a supervised running program. Reasons for dropout from the start-to-run program will be described and determinants for dropout will be analyzed by multivariate logistic regression models. Course and medical consumption and the associated direct and indirect costs will be described for injured runners.

Missing data will be completed by multiple imputation using the Multiple Imputation by Chained Equations (MICE) procedure, a technique in which missing values are replaced based on estimated relations in the dataset [37]. Ten multiple imputed datasets are generated, whereupon the results of those ten multiple imputed datasets will be combined using the rules given by Rubin [37].

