### The STR training program

The STR training program consists of three training sessions per week, one group training session supervised by a licensed athletic trainer and two individual training sessions. Each training session begins with a 15-minute warm-up and finishes with a 15-minute cool-down that consist of walking, stretching and relaxation exercises. The core of the training includes running program in which both running duration and intensity will be gradually increased. The STR program aims to prepare participants in 6 weeks for a 20-minute run without breaks. After the 6-week STR program, participants can choose to continue running in a way they prefer.

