### Injury definition

In the current study a running-related injury (RRI) is defined as any musculoskeletal ailment of the lower extremity or back that the participant attributed to running and hampers running ability for at least one week [14,18]. Hampering of running can be either a reduction in running speed, distance or duration, or an inability to run, both as a result of running-related pain.

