#### ***Web-based training log after the 6-week STR program***

After the 6-week STR program, a digital training log is sent to the participants every two weeks. This training log is a simplified version of the log that was used during the first six weeks. Information on running exposure, running surface, running-related pain and other sports activities is registered per week instead of at each training session. In this simplified training log, pain registration and monitoring of overuse injuries is similar to the methods used in the first six weeks. Participants who quit running after the STR program can indicate so, and only have to complete the information on other sports activities.

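### The running-injury incidence rate stops exposure by different rules for injured and non-injured runners, and its numerator is not tied to the same injuries or period.

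*Protocol article*

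**What the plan says.** All of the following is in the protocol article.

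- **Numerator** (Statistical analyses): incidence is calculated "as the number of new injuries reported per 1000 hours of running exposure". The text does not say whether this means first RRIs or every RRI, and it names no period.
- **Denominator** (Statistical analyses): hours are counted from the runner's start of the program "until an RRI is reported (injured runners) or until the end of the program (non-injured runners").
- **Repeat injuries** (Statistical analyses): one runner may have several RRIs. The rule is "In this case only the occurrence of the first RRI will be used for analysis". It stands in the paragraph on risk factors, not in the one on incidence.
- **Program and afterwards** (The STR training program): the program lasts 6 weeks. "After the 6-week STR program, participants can choose to continue running in a way they prefer".
- **Logging after week 6** (Web-based training log after the 6-week STR program): "After the 6-week STR program, a digital training log is sent to the participants every two weeks". That log still records running exposure and running-related pain.
- **Planning figures** (Sample size): 6,000 included, 20% dropout, 20% RRI incidence and 960 expected RRIs. No time window is attached to the 20%.

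**The concern.** A rate per 1000 hours is interpretable only if every injury counted could have arisen in the hours counted, and if the rule that ends a runner's hours does not depend on whether that runner is later injured. The definition as printed secures neither.

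The end-of-program limit is stated only for non-injured runners. Take two runners who both run on after week 6. One has a first RRI in week 20, and the other is still uninjured in week 20. Under the printed rule the first contributes an event and hours up to week 20, while the second stops contributing at week 6. The uninjured hours after week 6 are lost, but the injuries that arose in that period are not excluded. Limiting the count to first RRIs would not cure this. The period has to be matched as well.

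If repeat RRIs were also counted over hours that stop at the first one, the rate would rise further, in proportion to the mean number of RRIs per injured runner.

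At stake is a rate that other researchers will want to compare with their own. There is also a risk of carry-over. The article gives no other time-at-risk rule. If this one were used in the Cox model, everyone still at risk after week 6 would be a future case, and there would be no uninjured comparators in that period.

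**Working it through.** **Planning figures.** 6,000 × (1 − 0.20) = 4,800, and 4,800 × 0.20 = 960. Both agree with Sample size. The article states no rate per 1000 hours, so there is none to reproduce.

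**Inputs from the article.** 4,800 runners and 960 RRIs. Three sessions a week for 6 weeks give 18 sessions.

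**Assumed inputs (the article gives none).**
- 0.5 h of running per session, so H = 18 × 0.5 = 9 program hours.
- The 960 are first RRIs over the whole follow-up, with a share p = 30%, 50% or 70% falling in the program.
- An RRI in the program occurs on average halfway through, at 4.5 h.
- Running after week 6 is w = 0.5, 1.0 or 1.5 h a week.
- All runners are followed to week 52. That is 46 weeks after the program, with later RRIs on average 23 weeks into it. This simplifies the design, since the September group's questionnaires end at 26 weeks.

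**Formulas** (each × 1000):
- As written: 960 / [3,840 × 9 + 960p × 4.5 + 960(1 − p) × (9 + 23w)]
- Consistent 6-week: 960p / [(4,800 − 960p) × 9 + 960p × 4.5]
- Consistent 52-week: 960 / [3,840 × (9 + 46w) + 960p × 4.5 + 960(1 − p) × (9 + 23w)]

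**One case in full, p = 50% and w = 1.0.**
- As written: 34,560 + 2,160 + 15,360 = 52,080 h, so 960 / 52,080 = 18.4 per 1000 h.
- Consistent 6-week: 38,880 + 2,160 = 41,040 h, so 480 / 41,040 = 11.7.
- Consistent 52-week: 211,200 + 2,160 + 15,360 = 228,720 h, so 960 / 228,720 = 4.2.

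**All cases.** Ratios are from unrounded rates.

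| p | w (h/week) | As written | 6-week | Ratio | 52-week | Ratio |
|---|---|---|---|---|---|---|
| 30% | 0.5 | 19.3 | 6.9 | 2.81 | 7.0 | 2.8 |
| 30% | 1.0 | 16.7 | 6.9 | 2.44 | 4.1 | 4.1 |
| 30% | 1.5 | 14.7 | 6.9 | 2.15 | 2.9 | 5.1 |
| 50% | 0.5 | 20.6 | 11.7 | 1.76 | 7.1 | 2.9 |
| 50% | 1.0 | 18.4 | 11.7 | 1.58 | 4.2 | 4.4 |
| 50% | 1.5 | 16.7 | 11.7 | 1.43 | 3.0 | 5.6 |
| 70% | 0.5 | 22.1 | 16.7 | 1.32 | 7.3 | 3.0 |
| 70% | 1.0 | 20.5 | 16.7 | 1.23 | 4.3 | 4.8 |
| 70% | 1.5 | 19.2 | 16.7 | 1.15 | 3.0 | 6.3 |

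No repeat RRI is counted anywhere in this table. The excess comes from the unequal stopping rule alone.

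**The reading that works.** If all 960 are first RRIs within the program, hours are 3,840 × 9 + 960 × 4.5 = 38,880, and the rate is 960 / 38,880 = 24.7 per 1000 h. Numerator and denominator then match and nothing is inflated.

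**The case against.** The best defence is that the definition has the usual shape of a first-injury rate within the program. Hours end at an injury or at program end, and the first-RRI rule appears in the same section. On that reading there is no mismatch. This stands as a possible reading, but no sentence adopts it. The first-RRI rule belongs to the risk-factor analysis, the numerator has no period, and the logs go on recording both injuries and exposure. Nor does the shortness of an article explain the gap: it states a time-at-risk rule, and states it unequally.

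Four stronger readings are tempting, and the article does not support them.

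- **That every RRI is counted.** The text says neither all nor first.
- **That the rate is inflated by the simple factor one over the program's share of RRIs.** This holds the denominator at program hours, but runners injured later also bring their post-program hours.
- **That a week-6 cut would shrink the 960 expected RRIs, or that two sentences set conflicting Cox windows.** Sample size attaches no window to its 20%, and the Cox paragraph states no end of follow-up. Both windows are unstated, and neither is shown to be wrong.
- **That injuries starting in week 6 are lost.** An RRI is one that "hampers running ability for at least one week", so such cases can be confirmed only after the program. But pain registration continues by similar methods, and nothing says these cases are dropped.

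It is also fair that the rate is descriptive. No test or sample-size figure depends on it, and the primary objectives are health effects and RRI determinants.

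**Conclusion.** The point holds as an unequal and unmatched definition of time at risk. Followed literally, exposure depends on the outcome and the rate is too high. Under the assumed hours and timing it is 14.7 to 22.1 per 1000 h. That is about 1.15 to 2.8 times a consistent 6-week rate, and about 2.8 to 6.3 times a consistent 52-week rate. These ranges are illustrations. They vanish if the authors meant first RRIs within the program, and other hours or timing would move them. What does not depend on the assumptions is the direction of the error on the literal reading, and the fact that the text does not choose between the readings. Severity is moderate.

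**What to change.** In Statistical analyses, define incidence as first RRIs divided by running hours up to the first RRI or to a common censoring point that applies equally to injured and non-injured runners. Report it for the 6-week program and, separately, for the full log follow-up, with exposure extended to the last completed log for everyone. State which of these windows the Cox model uses, and which one the 960 expected RRIs in Sample size refer to.

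The cost is two or three sentences and a little extra analysis. The logs already collect exposure and injuries both during and after the program.

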## Methods/design

### Study design

The NLstart2run study is a multi-center prospective cohort study with a follow-up at 6, 12, 24 and 52 weeks, as can be seen in Figure 1. The study design, procedures and informed consent procedure were approved by the Medical Ethics Committee (no. 2012/350) of the University Medical Center Groningen (UMCG), the Netherlands. The trial is registered in the Netherlands Trial Registry (NTR3676).

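### The exposure rule gives uninjured runners a six-week end date but injured runners none, so follow-up depends on the outcome if injuries after week 6 are counted

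*Protocol article*

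**What the plan says.** The Statistical analyses section defines incidence as new injuries per 1000 hours of running. Exposure starts with the running program and lasts "until an RRI is reported (injured runners) or until the end of the program (non-injured runners". The uninjured branch has an end date and the injured branch has none. The program is the six-week Start to Run course; the section on the training program adds: "After the 6-week STR program, participants can choose to continue running in a way they prefer".

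On events, the same section says "It is possible for a single subject to sustain multiple RRIs during the study period", and then "In this case only the occurrence of the first RRI will be used for analysis". For the risk-factor model it says "For identification of risk factors for RRIs only data from the baseline questionnaire and the running log will be used", without restricting the log to its six-week part.

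Observation does not stop at week 6. The section on the later log states "After the 6-week STR program, a digital training log is sent to the participants every two weeks" and that "pain registration and monitoring of overuse injuries is similar to the methods used in the first six weeks"; running exposure is also recorded there, per week. Under Study design, "The NLstart2run study is a multi-center prospective cohort study with a follow-up at 6, 12, 24 and 52 weeks". The Follow-up questionnaires section gives 26 weeks in place of 24, and takes only the March starters to week 52.

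**The concern.** A rate and a Cox model both need the end of observation to be set without reference to whether the runner is later injured. Read literally, the rule breaks this. A first RRI in week 20 adds one event and 20 weeks of running. A runner who logs the same 20 weeks uninjured adds only six. After week 6 (on a calendar time scale) everyone still at risk is a runner who will be injured.

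Two results would suffer. The rate would combine a numerator from the longer period with a denominator drawn mostly from six weeks. In the Cox model, the later risk sets would compare cases only with other future cases, so a real risk factor would look weaker than it is. Identifying determinants of RRIs is one of the two primary objectives.

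**Working it through.** **1. The plan's own figures.** From Sample size: 6,000 × (1 − 0.20) = 4,800 runners at follow-up, and 4,800 × 0.20 = 960 RRIs. Both reproduce. The 20% has no period attached, so it does not show which event window was intended.

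**2. Two readings side by side.**

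- *One six-week window.* Uninjured means not injured by the end of the program, and only RRIs up to then count. This is ordinary administrative censoring and is unbiased.
- *Literal wording.* Any first RRI in the study period counts, with hours up to its report, while uninjured runners stop at week 6. Follow-up then depends on the outcome.

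**3. Size under the literal wording.** Assumptions, none of them given in the article: one running hour per week (this cancels in the ratios), no dropout, hazard λ₁ in weeks 0–6 and λ₂ afterwards, log follow-up to week T. Let p₆ and p_T be the proportions injured by week 6 and by week T.

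- λ₁ = −ln(1 − p₆)/6 and λ₂ = −ln[(1 − p_T)/(1 − p₆)]/(T − 6)
- Mean time per runner, all followed to T: F = p₆/λ₁ + (p_T − p₆)/λ₂
- Mean time under the literal rule: M = F − (1 − p_T)·T + (1 − p_T)·6
- Rates per 1000 hours: full 1000·p_T/F; six-week 1000·λ₁; literal 1000·p_T/M

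*Example A, constant hazard, 20% injured by week 52.* λ = −ln(0.8)/52 = 0.00429. F = 0.2/λ = 46.61. M = 46.61 − 0.8 × 52 + 0.8 × 6 = 9.81. Literal rate 0.2/9.81 = 20.4 per 1000 hours against 4.3, a ratio of 4.75.

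*Example B, 15% by week 6 and 20% by week 52.* λ₁ = 0.02709 and λ₂ = 0.001318, so F = 5.54 + 37.94 = 43.48. M = 43.48 − 41.6 + 4.8 = 6.68. Literal rate 30.0, against 4.6 for full follow-up (ratio 6.5) and 27.1 for a six-week window (ratio 1.1).

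The hazard ratios below come from simulated Cox fits on calendar time: 4,800 runners, one binary factor present in half, 30 runs per row.

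| Injured by week 6 → by week T | Full rate | Six-week rate | Literal rate | Literal vs full | Literal vs six-week | HR 1.5 becomes | HR 2.0 becomes |
|---|---|---|---|---|---|---|---|
| 2.5% → 20%, T = 52 | 4.29 | 4.29 | 20.39 | 4.75 | 4.75 | 1.06 | 1.14 |
| 10% → 20%, T = 52 | 4.47 | 17.56 | 25.16 | 5.63 | 1.43 | 1.24 | 1.43 |
| 15% → 20%, T = 52 | 4.60 | 27.09 | 29.96 | 6.51 | 1.11 | 1.32 | 1.75 |
| 10% → 20%, T = 26 | 8.82 | 17.56 | 29.96 | 3.40 | 1.71 | 1.25 | 1.46 |
| 20% → 30%, T = 52 | 7.53 | 37.19 | 39.34 | 5.22 | 1.06 | 1.32 | 1.57 |

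**4. A cohort closer to the schedule.** With half the runners followed 26 weeks and half 52, the literal rate is 3.1 to 5.3 times the full-follow-up rate. Against a six-week rate it runs from about 1.1 times, when most RRIs are early, to 3.9 times under a constant hazard. A true HR of 1.5 is estimated as 1.06 to 1.37, and 2.0 as 1.20 to 1.80.

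**5. The same data with a common window.** In the table's scenarios, following everyone to week T gave 1.46–1.51 for a true 1.5 and 1.97–2.04 for a true 2.0. Cutting everyone at week 6 gave 1.46–1.53 and 1.94–2.06. The distortion therefore comes from the unequal end dates.

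**The case against.** The tempting stronger reading is that the plan does count RRIs after week 6, so that its incidence and hazard ratios will be wrong. The documents do not support that. No sentence says later RRIs enter the rate or the Cox model. The mention of the study period serves to say that only the first RRI is used. The later log has other purposes: an RRI registered in the log triggers the questionnaire on treatment, absence and costs, and sports participation after the course is of interest in itself. A single six-week window is a plausible reading and an unbiased one.

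Several narrower objections also have force:

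- The exposure sentence stands in the incidence paragraph. The Cox paragraph gives neither a time axis nor a censoring rule, so the effect on hazard ratios depends on the same times being used there. On a running-hours axis the risk sets after week 6 are not made up purely of cases, although simulation with varying hours still gave 1.14–1.29 for a true 1.5 and 1.33–1.57 for a true 2.0.
- The log has no stated end date; 26 and 52 weeks are borrowed from the questionnaires. Runners who quit have no later hours to lose. If half quit after week 6, the constant-hazard rate ratio falls from about 3.9 to about 2.7.
- The size depends on the hazards assumed. With about 15% injured by week 6 and 23–26% overall, one simulation gave attenuation only to about 1.43 and 1.77.

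An exact censoring date can often be left to the analysis plan. Here, though, the article does state a rule, and states it differently for the two groups. The benign reading has to supply a limit for injured runners that the sentence omits and to take the study period as the program. That part of the concern stands.

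**Conclusion.** The concern holds as a conditional one. The stated rule sets unequal ends of observation and does not reconcile the program with the study period. Under its literal reading, the incidence rate is too high and, if the Cox model shares the exposure times, hazard ratios move towards 1. The direction was the same in every scenario tried.

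The size rests on assumed post-program hazards and log length. For a cohort split between 26 and 52 weeks, the rate is about 3 to 5 times the full-follow-up rate (up to 6.5 if everyone is followed for 52 weeks), but from about 1.1 to nearly 4 times a six-week rate. Hazard ratios of 1.5 and 2.0 are estimated as about 1.06–1.37 and 1.20–1.80. If only RRIs within the six weeks count, there is no bias and the only defect is the wording. The expected 960 RRIs are arithmetically correct, but whether they are reached depends on the window.

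**What to change.** Reword the exposure sentence so that injured and uninjured runners share one end of observation that does not depend on the outcome, and state that it governs both the incidence rate and the Cox model. Either version is sound:

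- Count first RRIs and running hours only to the end of week 6, for everyone.
- Count first RRIs and logged running hours to a stated common end of log follow-up, or to the last completed log, for everyone. The log's end date must then be given.

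One window is enough; two analyses are not required. It would help to attach the same period to the 20% in Sample size.

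The change costs one sentence and no new data. The reported incidence may be lower than under the literal rule, and a six-week window may yield fewer events. For example, if only 10% were injured by week 6, 4,800 × 0.10 = 480 RRIs would be available in place of 960, which at 10 per factor supports 48 factors rather than 96.

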### Sample size

Based on previous studies on RRIs among novice runners, an injury incidence of 20% is expected [7,14,18]. Taking into account a dropout rate of 20% [6,7,14,18,19], the inclusion of 6,000 participants will lead to approximately 4,800 participants at follow-up. With an RRI incidence of 20%, a total of 960 RRIs are expected. Taking into account the need of a minimum of 10 RRIs per risk factor analyzed in a multivariate model, this is sufficient for accounting for the multivariate nature of RRIs [15,20].

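### The named Cox, logistic and repeated-measures ANOVA analyses make no allowance for clustering by training group or location, so intervals for group-shared factors and for mean health change may be too narrow

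*Protocol article*

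**What the plan says.** Under Study design the article states: "The NLstart2run study is a multi-center prospective cohort study". The section on the STR training program describes three sessions a week for six weeks: "one group training session supervised by a licensed athletic trainer and two individual training sessions". Afterwards runners continue as they like. Courses start in March and in September (Study population).

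Under Statistical analyses, three model families are named:
- For injury determinants: "Potential risk factors for RRI will be entered into a multivariate Cox regression prediction model". Hazard ratios with 95% confidence intervals follow, and the candidate factors come from the baseline questionnaire and the running log.
- For dropout: "determinants for dropout will be analyzed by multivariate logistic regression models".
- For health effects: a repeated-measures ANOVA of the baseline and follow-up questionnaires.

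No group, trainer or site term, frailty, random effect, stratification or robust variance is mentioned. The Sample size section contains no design effect.

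**The concern.** Runners in one group share a trainer, a place and a start date, and one session a week. Injury, dropout and health change may therefore be more alike within a group than between groups. In their standard form, Cox and logistic models assume independent subjects. A repeated-measures ANOVA deals with correlation within a person, not between persons in the same group.

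Run in that form, the models would understate the standard error of any factor that is itself shared or correlated within groups, and of the mean change in health. The log records surface, frequency, duration and perceived exertion, which are plausibly alike within a group at least for the supervised session. These are also the factors a programme organiser could alter, and the Discussion expects the study to find modifiable ones. The risk is that a training-related factor is declared a determinant of injury or dropout on an interval that is too short.

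**Working it through.** **The article's own figures.** The Sample size section says that "the inclusion of 6,000 participants will lead to approximately 4,800 participants at follow-up" and that "a total of 960 RRIs are expected". Check: 6,000 × (1 − 0.20) = 4,800; 4,800 × 0.20 = 960; at 10 events per factor, 960 / 10 = 96 factors. These reproduce exactly.

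**Inputs for clustering.** The number m of analysed runners per group and the ICC of the outcome are not given. Both are assumed: m = 10 to 30, ICC = 0.01 to 0.05.

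**Purely group-level factor.** Design effect DE = 1 + (m − 1) × ICC. The correct interval is √DE times the naive one. The actual error of a nominal 5% test is 2 × [1 − Φ(1.96/√DE)].

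| m | ICC | DE | width × | actual error |
|---|---|---|---|---|
| 10 | 0.01 | 1 + 9 × 0.01 = 1.09 | 1.04 | about 6% |
| 20 | 0.02 | 1 + 19 × 0.02 = 1.38 | 1.17 | about 9.5% |
| 20 | 0.05 | 1 + 19 × 0.05 = 1.95 | 1.40 | about 16% |
| 30 | 0.05 | 1 + 29 × 0.05 = 2.45 | 1.57 | about 21% |

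**Other factors.** For a covariate whose own within-group correlation is ICC_x, approximately DE = 1 + (m − 1) × ICC × ICC_x. At m = 20 and ICC = 0.02:
- ICC_x = 0 (varies freely within groups): DE = 1.00, width × 1.00.
- ICC_x = 0.1: DE = 1 + 19 × 0.02 × 0.1 = 1.038, width × 1.02.
- ICC_x = 0.5 (partly shared): DE = 1 + 19 × 0.02 × 0.5 = 1.19, width × 1.09.

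Even at m = 30 and ICC = 0.05, ICC_x = 0.1 gives DE = 1.145 and width × 1.07.

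**Simulation check.** Ordinary logistic regression was fitted to 240 groups of 20 (4,800 runners) with an event rate near 20%, latent-scale ICC 0.03 and 1,000 runs. Naive 95% intervals covered the truth 90.9% of the time for a group-level covariate and 94.6% for an individual-level one.

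**Health change.** Write the score of person i in group j at time t as mean(t) + group effect u_j + person effect + error. In a within-person difference, u_j cancels, so a constant group effect leaves the time effect and its standard error untouched. Only a group effect that differs between times, a group-by-time effect, makes changes alike within a group. The DE formula then applies with the ICC of the change.

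**The case against.** The strongest objection is that this argues from silence in a condensed article. Naming a Cox model is compatible with robust errors or a frailty, and a fuller plan may specify one. It stands this far: a reader might infer that the plan declares participants independent, and the text does not say so. It does not dispose of the point. The same section is specific elsewhere: it fixes the number of imputed datasets and the pooling rule, and handles repeated injuries in one runner by using only the first. The dependence built into the programme is left out, and models run as named would ignore it.

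A second objection is that most candidate factors are personal: demographics, BMI, injury history, footwear, activity, motivation and perceived health. No trainer or group variable is listed, and surface and exertion are logged by each runner. This stands. A reader might infer that all the intervals are too narrow; the working contradicts that.

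Third, the ICC may be small, since two of three weekly sessions are individual and the grouping lasts six weeks. Not every group member need be in the study either. The Background puts annual enrolment above 8,000; 4,800 / 8,000 = 60%, so a group of 20 might contribute 12 analysed runners. At ICC 0.02, DE = 1 + 11 × 0.02 = 1.22 and the error is about 7.6% instead of 9.5%. This is fair: the size is illustrative.

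Finally, a reader might extend the point to injury incidence or to the sample size. The text plans incidence as a rate per running hour and states no interval for it. Dividing the 960 events by the largest design effect above still leaves 960 / 2.45 ≈ 392, enough for 39 factors under the article's rule.

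**Conclusion.** The point holds in limited form. The article describes participants nested in trainer-led groups at several centres and names three analyses without any allowance for that nesting. The intervals at risk are those for factors shared or correlated within groups, together with inference on mean health change. Those for age, BMI, previous injury and similar individual-level factors are close to correct.

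For a purely group-level factor the design effect would be 1.09 to 2.45 under the assumed 10 to 30 runners and ICC of 0.01 to 0.05. Factors logged by each runner and only partly shared would fall below that. For health change, the size depends on how far the change itself is shared within groups, which the article does not show. The point is worth correcting because the remedy is cheap; it does not undermine the cohort or its sample size.

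**What to change.** 1. Record the training group or location of every participant. The article does not say that registration for the course captures this, so it should be collected explicitly; it may be hard to recover later.
2. In the Cox and logistic models, state that standard errors are clustered on this identifier. The hazard and odds ratios keep their present meaning; a random intercept in the logistic model would change the odds ratio to a group-conditional one.
3. For health change, use cluster-robust errors on change scores, or a mixed model with a group-by-time random effect. A group random intercept alone does not correct the time effect, as shown in the working.

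Stratifying the Cox model by start month is not needed for this purpose, and it would remove any hazard ratio for start month.

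The cost is one identifier to collect, a sentence per model, and slightly wider intervals for some factors.
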